### Study aims

1: Convene a Steering Committee of key stakeholders and recruit implementation sites to provide oversight for the development of processes for communication, decision-making, coordination, and distribution of CPAP/O_2_ helmet solutions for non-invasive ventilation at the eight COVID-19 treatment and isolation centers.

2: Use the integrated Promoting Action on Research Implementation in Health Services (i-PARiHS) framework to guide needs assessment, perform stakeholder analysis of the treatment centers’ capacity to use high-flow oxygen therapy to treat COVID-19 patients, and use the findings to develop a context-specific, practice facilitation strategy to implement the CPAP/O_2_ helmet solution for non-invasive ventilation.

3: Build infrastructure to support training and data monitoring processes and develop implementation protocols to evaluate the adaptability of the strategy for implementing use of CPAP/O_2_ helmets for non-invasive ventilation.

4: (a) Train healthcare workers; distribute a CPAP/O_2_ helmet solution for non-invasive ventilation, pilot test the practice facilitation [implementation] strategy, and assess feasibility of its use and acceptability; (b) estimate the altered risk of SARS-CoV-2 infection among healthcare workers associated with the use of CPAP/O_2_ helmets for non-invasive ventilation.

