### Is the use of the CPAP/oxygen helmet associated with a greater risk of COVID-19 infection among healthcare workers? (specific aim 4 b)

Healthcare personnel are at increased risk of acquiring COVID-19 infection [18]. Studies of other respiratory pathogens have documented increased transmission risk associated with aerosol generating procedures (AGP), many of which can generate both large droplets and small particle aerosols. Non-invasive ventilation is considered an AGP, but it is postulated that helmet ventilation may be associated with less risk of transmission of respiratory pathogens via aerosolization given containment in the helmet and negligible air dispersion.

A case-control study design will be implemented. We will enroll clinical and environmental hospital staff who have exposure to SARS-CoV-2 via provision of direct patient care or environmental care at the eight CircumVent study sites. Consenting and eligible health care workers will complete baseline testing for SARS-CoV-2-specific antibodies and complete an exposure assessment form summarizing risk factors and potential COVID-19 exposures in the prior 1 month. All healthcare workers assessed at time 0 comprise the retrospective study cohort. Individuals who test negative for COVID-19 antibodies at time 0 will be invited to participate in the prospective study. They will be followed for up to 6 months during which they will complete monthly encounter forms to assess community and healthcare-related exposures and to document any PCR-confirmed diagnoses of SARS-CoV-2 infection. However, the study will be censored and exit interview and a second sample for SARS-CoV-2 antibodies will be obtained if and when COVID-19 vaccine becomes available at the designated COVID-19 treatment centers.

In the retrospective study, a case is defined by seropositivity to SARS-CoV-2-specific antibodies, and a control is defined by seronegativity to SARS-CoV-2-specific antibodies. In the prospective study, a case is defined by seropositivity to SARS-CoV-2-specific antibodies, or a clinical case of SARS-CoV-2 infection confirmed by PCR testing, and a control is defined by the absence of infection, either by SARS-CoV-2 PCR or SARS-CoV2 specific antibodies.

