#### Quantitative data analysis

Both the retrospective and nested prospective case-control studies will compare differences in exposures and risk factors observed between cases and controls using Chi-square or Fisher’s exact test. All tests will use 2-tailed probability, with *P* values < 0.05 considered statistically significant. Variables that are statistically significant will be included in forward logistic regression analysis to arrive at independent measures of association.

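### Aim 4b's single helmet question is tested in two case-control studies at P < 0.05, on the same footing as every other exposure, and nothing says which result decides

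*Protocol article*

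**What the plan says.** Under Study aims, aim 4(b) is to "estimate the altered risk of SARS-CoV-2 infection among healthcare workers associated with the use of CPAP/O_2_ helmets for non-invasive ventilation". The section on specific aim 4b puts this as a single question about the helmet and sets up two studies to answer it.

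- **Retrospective study.** "All healthcare workers assessed at time 0 comprise the retrospective study cohort". Cases are those with antibodies at that point and controls are those without. The exposure form looks back one month.
- **Prospective study.** Only workers without antibodies at time 0 are invited. They complete monthly exposure forms for up to 6 months. A case is a new positive antibody test or a PCR-confirmed infection. Follow-up ends early if a vaccine becomes available at the centres.

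The Quantitative data analysis section then gives one rule for both: "Both the retrospective and nested prospective case-control studies will compare differences in exposures and risk factors observed between cases and controls". Each variable is tested singly, by a chi-square or an exact test. The threshold is the same everywhere: "All tests will use 2-tailed probability, with *P* values < 0.05 considered statistically significant". Model building follows from it: "Variables that are statistically significant will be included in forward logistic regression analysis to arrive at independent measures of association". That section does not mention the helmet.

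**The concern.** The aim is specific but the analysis rule is generic. Helmet use is handled like any incidental community or workplace exposure, and it is examined twice with no statement of which result answers the aim. If it is significant in one study and not in the other, the plan supports either report, and the choice can be made after the data are seen.

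The two results are not interchangeable replicates. A worker with antibodies at time 0 may have been infected well before the month covered by the exposure form, so the retrospective comparison can relate an exposure to an infection that preceded it. The prospective comparison starts from workers without antibodies and records exposure as follow-up proceeds.

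The screening rule adds a second difficulty. Helmet use reaches the logistic model only if its univariate test is significant. Otherwise the plan yields no adjusted estimate for the one exposure that the aim is about.

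**Working it through.** **Inputs from the article.** Two-sided 0.05 per test with no adjustment stated; two studies analysed alike; univariate screen, then forward logistic regression. The article gives no sample size, power or number of exposures for aim 4b, so there is no derived figure to reproduce.

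**Assumptions.** Helmet exposure occurs, and can be tested, in both studies. The power p per study is assumed over a range. Independence between the studies is assumed unless stated otherwise.

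**1. False helmet signal.** If helmet use has no association with infection, the chance of at least one significant result is

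1 − (1 − 0.05)² = 1 − 0.9025 = 9.75%.

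Positive correlation between the two test statistics lowers this. Simulation with correlated normal statistics (200,000 draws) gives 9.1% at correlation 0.5 and 7.7% at 0.8. One named contrast at 0.05 gives 5%.

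**2. Disagreement on significance.** The chance that exactly one study is significant is 2p(1 − p).

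| Chance of significance in each study, p | Exactly one significant |
|---|---|
| 0.05 (no effect) | 9.5% |
| 0.30 | 42% |
| 0.50 | 50% |
| 0.80 | 32% |
| 0.90 | 18% |

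The chance of both being significant in opposite directions, with no effect, is 2 × 0.025 × 0.025 = 0.125%.

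**3. Helmet use lost at the screen.** With univariate power p in a study, helmet use fails to reach that study's model with probability 1 − p: 70%, 50% and 20% at p = 0.30, 0.50 and 0.80.

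**4. Other exposures.** Let k be the assumed number of exposures per study, all without effect. The chance of at least one significant result over both studies, with independent tests, is 1 − 0.95^(2k). The last column allows a correlation of 0.5 within each study.

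| k | Independent | Correlation 0.5 |
|---|---|---|
| 5 | 40.1% | 33% |
| 10 | 64.2% | 49% |
| 20 | 87.1% | 66% |

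With independent tests the rate passes one half at k = 7 (1 − 0.95¹⁴ ≈ 51%).

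Forward selection removes little. In a simulation with assumed values (400 workers per study, 20% cases, 10 exposures without effect, 30% exposure prevalence, 400 replicates), at least one variable passed the screen in 61–62% of replicates. At least one remained after forward selection in 60–62%.

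**The case against.** The strongest reply is that this is mostly an omission. A condensed article need not set out a testing hierarchy, and a plan that is not shown may do so. The wider study is a feasibility project whose named implementation outcomes do not include infection risk, aim 4b is worded as estimation, and unadjusted testing is acceptable in an exploratory search for risk factors. Much of that stands: a missing multiplicity adjustment would not by itself be a finding. What remains is what the article does state, namely one significance rule for all variables in both studies, with the survivors presented as independent associations and the helmet subject to the same screen.

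Three further limits also stand.

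- A reader might infer that the two studies are apt to give opposite answers. The document does not support that. The disagreement calculated here is significant against non-significant, and a non-significant result is not evidence of the reverse effect.
- A reader might infer that false risk factors are likely. That rests on an assumed number of exposures, all without effect. At correlation 0.5 the rate for 5 or 10 exposures is below one half.
- The double test exists only if helmet exposure can be assessed retrospectively. The article does not date time 0 relative to helmet deployment. If time 0 comes first, there may be little or no helmet exposure to compare in that study. The prospective study is also drawn from the retrospective controls, so independence is an approximation.

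**Conclusion.** The point holds for the helmet question. The article tests one question in two studies of different design and does not say which result decides. The false-signal rate is up to 9.75% instead of 5%, provided that the tests are independent and helmet exposure is testable in both; correlation brings it to 7.7–9.1% over the values tried. This inflation is modest. The larger weaknesses are the freedom to choose between discordant results, the uncertain timing of infection in the retrospective study, and the possibility that helmet use never enters the adjusted model.

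For the other exposures, chance findings are possible, but the document gives no basis for saying how probable they are. The matter should be corrected before analysis; it does not invalidate the study.

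**What to change.** Add to Quantitative data analysis:

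1. The single primary contrast for aim 4b is helmet exposure versus none in the prospective study, reported as an adjusted odds ratio with 95% CI and tested at two-sided 0.05.
2. Helmet use stays in the logistic model whatever its univariate P value.
3. The retrospective helmet comparison is supportive only and cannot overturn the primary result.
4. All other exposure comparisons, in both studies, are exploratory and reported as estimates with 95% CIs.

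This sets the error rate for the helmet question at 5%. A false-discovery-rate adjustment for the exploratory comparisons is optional.

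The cost is a few sentences, with no new data or participants. Fewer secondary factors can be called significant, and a signal seen only in the retrospective study cannot be presented as the answer. The primary contrast may also be imprecise if vaccine availability shortens prospective follow-up and leaves few cases; the confidence interval will show this.

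### Aim 4b: helmet use gets an adjusted estimate only if it passes a P < 0.05 screen and forward selection, so the promised risk estimate can be missing, exaggerated or poorly adjusted

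*Protocol article*

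**What the plan says.** All references are to the protocol article.

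- **Study aims, aim 4(b):** the study will "estimate the altered risk of SARS-CoV-2 infection among healthcare workers associated with the use of CPAP/O_2_ helmets for non-invasive ventilation". That is one exposure and one effect to estimate.
- **Section on specific aim 4 b:** the heading puts the same question: "Is the use of the CPAP/oxygen helmet associated with a greater risk of COVID-19 infection among healthcare workers". The design is observational: "A case-control study design will be implemented". On enrolment: "We will enroll clinical and environmental hospital staff who have exposure to SARS-CoV-2", where exposure may come through direct patient care or environmental care.
- **Quantitative data analysis:** the retrospective and nested prospective studies "will compare differences in exposures and risk factors observed between cases and controls using Chi-square or Fisher’s exact test", two-sided, with P "values < 0.05 considered statistically significant". The model-building rule follows: "Variables that are statistically significant will be included in forward logistic regression analysis to arrive at independent measures of association".

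No sentence keeps helmet use, or any confounder, in the model regardless of its P value.

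**The concern.** The stated rule suits a search for risk factors among many candidates. Aim 4b is a different task: it has one exposure, chosen in advance, whose effect is to be estimated with adjustment. Under the rule, helmet use is one candidate among the rest. This has three consequences.

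1. **Missing estimate.** If the crude helmet test gives P of 0.05 or more, or helmet use fails at the forward step, there is no adjusted helmet odds ratio.
2. **Biased estimate.** If helmet use gets through, it does so because the observed association was large enough. The reported odds ratio is then on average too far from 1, and a standard error that ignores the selection is too small.
3. **Adjustment by P value.** Whether leaving out a confounder biases the helmet estimate depends on its links with both helmet use and infection. Its own crude P value does not settle that. Staff role is the obvious case, because enrolment mixes clinical and environmental staff.

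At stake is the study's healthcare-worker safety question. The article's Abstract raises that concern, and its Discussion offers the findings as pilot data for scale-up.

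**Working it through.** The article gives no sample size, event count or effect size for Aim 4b, so there is no figure of its own to reproduce. Every input below except the 0.05 two-sided threshold is an assumption.

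**1. Chance of passing the screen.** Assume risk 25% in the unexposed, 30% of workers exposed, true odds ratio 1.5, uncorrected chi-square.

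- Odds in the exposed = (0.25/0.75) × 1.5 = 0.50, so risk p1 = 0.50/1.50 = 0.333. Difference d = 0.0833. Overall risk = 0.3 × 0.333 + 0.7 × 0.25 = 0.275.
- SE0 = sqrt[0.275 × 0.725 × (1/n1 + 1/n0)]; SE1 = sqrt[0.333 × 0.667/n1 + 0.25 × 0.75/n0].
- Chance of passing = 1 − Φ[(1.96 × SE0 − d)/SE1].

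| Workers (exposed / unexposed) | SE0 | SE1 | Chance of passing |
|---|---|---|---|
| 200 (60 / 140) | 0.0689 | 0.0710 | 23% |
| 400 (120 / 280) | 0.0487 | 0.0502 | 40% |
| 800 (240 / 560) | 0.0344 | 0.0355 | 67% |

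**2. Exaggeration when it passes.** At 200 workers the smallest significant difference is about 1.96 × 0.0689 = 0.135. With overall risk at 0.275 this means about 0.3695 against 0.2345, an odds ratio of (0.3695/0.6305)/(0.2345/0.7655) = 1.9. A true odds ratio of 1.5 therefore cannot be reported near its real value. By simulation, the geometric mean odds ratio among studies that pass is 2.3, 1.9 and 1.6 at 200, 400 and 800 workers.

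**3. The full two-stage rule.** A separate simulation (1,000 replicates per setting, one binary confounder present in 50%, other assumed risks) applied the screen and then forward entry at 0.05. It compared this with a model that always holds helmet use and the confounder. Results are for 200 / 400 / 800 workers.

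| Setting | Helmet kept by the rule | Mean OR when kept | Confounder kept | Mean OR, fixed model |
|---|---|---|---|---|
| True OR 1.5, modest confounding | 24 / 43 / 65% | 2.57 / 2.02 / 1.72 | 22 / 38 / 63% | 1.51 / 1.53 / 1.51 |
| True OR 0.5, masked by a confounder | 13 / 23 / 45% | 0.28 / 0.37 / 0.41 | 36 / 60 / 92% | 0.49 / 0.49 / 0.49 |
| True OR 1, confounded | 6 / 5 / 4% | 2.25 / 1.76 / 1.51 | 21 / 43 / 74% | 1.02 / 1.00 / 1.00 |

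In the masked setting the fixed model finds the effect significant in 31 / 58 / 87% of replicates, against 13 / 23 / 45% in which the rule keeps helmet use at all.

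**4. What an unadjusted confounder can do.** Suppose helmets have no effect, direct care doubles the odds of infection, all helmet users but only half of the others give direct care, and risk without direct care is 25%. Risk with direct care is 0.667/1.667 = 0.40. Risk in non-users is 0.5 × 0.40 + 0.5 × 0.25 = 0.325. The crude odds ratio is (0.40/0.60)/(0.325/0.675) = 1.38. With 15% risk it is 1.37. If role fails the screen, this spurious association stays in the helmet estimate.

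**The case against.** - **The question is not left wholly unanswered.** A reader might infer that Aim 4b could end with no answer. The article does not support that: exposures are compared between cases and controls by Chi-square or Fisher's exact test whatever the model does. What can be lost is the adjusted estimate. This limit stands.
- **The text does not say *only*.** It says that significant variables will be included, not that nothing else may be. Exclusion of the rest is the natural reading, since this is the sole route given to independent measures of association, but it is a reading. A covariate list may also sit in a fuller document, and its absence here is no fault. The criticism is of the selection rule that is stated.
- **The article does not say how a null result will be read.** A dropped helmet term could be taken as reassurance, but nothing shows that it will be.
- **Helmet exposure is not defined.** One might argue that environmental staff are unlikely to operate helmets. The article does not say that exposure means operating the device, so the role example is a scenario only.
- **Form contents are not listed.** Community exposure is named as recorded; personal protective equipment and other aerosol-generating procedures are not. It cannot be assumed that these are available.
- **The pass rates are simply the power of a chi-square test.** A fixed model does not make a small study informative. It does ensure that an estimate and interval are reported. A continuity correction lowers the pass rates further, to roughly 18%, 36% and 64%. In the null setting simulated, false retention stayed near 5%, so the main fault lies in estimation rather than in false-positive rate.

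These points narrow the wording and the severity. They do not remove the mismatch between an aim that promises an estimate and a rule that does not guarantee one.

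**Conclusion.** The point holds in this form. The stated selection rule does not secure the adjusted helmet estimate that Aim 4b promises. When it does yield one, the estimate is on average exaggerated, its standard error is too small, and the confounders behind it were chosen by P value.

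The sizes rest on assumed sample size, risks, exposure share and confounder strength. They show that the effect can be large in studies of a few hundred workers and shrinks as numbers grow. They do not predict this study's result.

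Severity is should-fix. A reader might rate it higher because it concerns safety. However, Aim 4b is the second part of the fourth aim in a study of feasibility, adaptability and acceptability, and the rule does not touch those outcomes.

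**What to change.** Replace the sentence on forward logistic regression with wording such as:

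> Helmet exposure is kept in the logistic model whatever its P value, together with a fixed set of confounders chosen on subject-matter grounds from the data collected: site, staff role, direct patient care, community exposure and, where collected, use of personal protective equipment and other aerosol-generating procedures. The adjusted odds ratio for helmet exposure with its 95% confidence interval is the Aim 4b result. A non-significant result is not treated as evidence of no added risk. Screening and forward selection are used only for a separate list of other risk factors, labelled exploratory.

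**Cost.** This changes the analysis text and needs no new data for items already recorded. Whether every listed item is recorded should be checked against the forms. The fixed confounders use a few degrees of freedom; if cases are few, penalised (Firth) logistic regression can be used.

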## Discussion

The COVID-19 pandemic will subside, but its effect on health systems will likely linger, particularly for African countries whose healthcare infrastructure is vulnerable. In this paper, we describe a non-invasive ventilation approach to management of COVID-19 in Nigeria using CPAP/O_2_ helmets. There are three key strengths in this study. First, this study uses a well-established implementation science framework (I-PARiHS) to assess the implementation climate, explore factors and support systems required for successful implementation of CPAP/O_2_ helmet solutions for non-invasive ventilation and to develop an evidence-based implementation strategy (practice facilitation) for the use of the helmets across eight COVID-19 treatment centers in Nigeria. Whereas extant literature in LMICs show that the uptake of evidence-based interventions is a desired implementation research outcome, there is limited evidence of interventions targeted at addressing care of COVID-19 patients with acute respiratory failure in Africa. Second, if successfully implemented, findings from this study will serve as pilot data for scaling up this strategy in other LMICs. The proposed project is in a position to collaborate with other groups to provide technology platforms to deliver training and support resources. Finally, the innovation that will be derived from the sourcing and using of these CPAP/O2 helmet solutions for non-invasive ventilation in Nigeria will serve as a model to other countries in Africa. The CPAP/O_2_ helmets can also be a major treatment for childhood pneumonia, the number one killer of children in low-income countries like Nigeria [24].

## Data Availability

The study PI and key investigators will have access to all data. Data access to other researchers will be considered on a case-by-case basis, upon reasonable request.

## Abbreviations

CPAP: Continuous positive airway pressure
COVID-19: Coronavirus disease 2019
SARS-CoV-2: Severe acute respiratory syndrome coronavirus type 2
NIMR: Nigeria Institute for Medical Research
NCDC: Nigeria Center for Disease Control
O_2_: Oxygen
i-PARiHS: Integrated Promoting Action on Research Implementation in Health Services
LMIC: Low- and middle-income countries
